**Figure 1 F1:**
[figure not shown]
Organogram of the national quality improvement program palliative care.

An existent set of quality indicators measured among patients and bereaved relatives will be used for the effect evaluation [20]. The inclusion and exclusion criteria for patients and bereaved relatives are described in Additional files 2 and 3. Per trajectory we aim to include 15–20 patients and 30–40 bereaved relatives in each assessment period. As there are two assessment periods for the approximately 17 planned trajectories per year, this will result into a minimum of about 510 participating patients and 1020 participating bereaved relatives per year, which gives a total number of about 2040 patients and 4080 bereaved relatives over four years.

For the process evaluation, data will be collected among professionals. For each implementation trajectory, the project manager will be interviewed and a group interview will be done with other stakeholders involved. Assuming 17 implementation trajectories per year over four years, this will result in 68 interviews with project managers and 68 group interviews with stakeholders.

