**Methods/Design:**

This paper presents the protocol of the evaluation study consisting of a quantitative effect evaluation and a qualitative process evaluation. The effect evaluation has a pre-test post-test design, with measurements before implementation (month 0) and after implementation (month 9) of a best practice. Patients are eligible if they have a life expectancy of less than six months and/or if they are undergoing palliative treatment and provided they are physically and mentally capable of responding to questionnaires. Bereaved relatives are eligible if they have been involved in the care of a deceased patient who died after a sickbed between six weeks and six months ago. Three types of measurement instruments are used: (1) numerical rating scales for six symptoms (pain, fatigue, breathlessness, obstipation, sadness and anxiety), (2) the Consumer Quality Index Palliative Care - patient version and (3) the version for bereaved relatives.

The process evaluation consists of analysing implementation plans and reports of the implementation, and individual and group interviews with healthcare professionals. This will be done nine to eleven months after the start of the implementation of a best practice.

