### Study population

All implementation trajectories receiving a grant in the National Quality Improvement Programme will participate in the evaluation study. Within the participating organizations, data will be collected from patients and bereaved relatives (see Figure 1). In implementation trajectories with more than five participating organizations, a purposive sample will be selected of care organizations with the highest number of patients meeting the inclusion criteria and representing all the different settings involved in the specific implementation trajectory.

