### Effect evaluation

Pre-test and post-test measurements will take place in the effect evaluation, in month 0 and month 9 respectively (see Figure 2). During these two measurement months, eligible patients and bereaved relatives will be asked to participate.

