#### Data analysis

Descriptive statistics (frequencies, percentages and means) will be used to analyse background characteristics.

The effects of the separate implementation trajectories (research question 2) will be analysed using descriptive analyses as well as univariate analyses (with paired t tests or McNemar’s test). To assess the differences between pre-test and post-test measurements for the whole programme (research question 1), multilevel analysis will be used, including the levels of the participating care networks or care organizations, and the type of best practice. SPSS, STATA and ML-WIN will be used for the statistical analysis.

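### The univariate tests for separate trajectories take no account of organisation, so any shift in organisation mix between month 0 and month 9 enters the trajectory's pre-post difference

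*Protocol article*

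**What the plan says.** All statements are in the protocol article.

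- **Target.** Study population: "Per trajectory we aim to include 15–20 patients and 30–40 bereaved relatives in each assessment period". No split by organisation or setting is given.
- **Several organisations and settings.** The same section: "In implementation trajectories with more than five participating organizations, a purposive sample will be selected of care organizations", chosen for high numbers of eligible patients and for "representing all the different settings involved in the specific implementation trajectory". So mixed settings within a trajectory are expected.
- **Recruitment at each measurement.** Effect evaluation: "During these two measurement months, eligible patients and bereaved relatives will be asked to participate".
- **Analysis.** Effect evaluation, Data analysis: the separate trajectories "will be analysed using descriptive analyses as well as univariate analyses", with paired t tests or McNemar's test as the named tests. Multilevel analysis, with care networks or care organisations as levels, is named only for research question 1.
- **Mode of completion.** Effect evaluation, Data collection: inpatients complete the patient CQ Index with a trained interviewer. Patients at home receive it by post and get no reminder. All bereaved relatives receive theirs by post.

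**The concern.** A pre-post difference at trajectory level mixes two things: change inside each organisation, and change in how much each organisation contributes. Only the first is an effect of the best practice. The plan fixes neither the contributions nor an analysis that separates the two.

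Organisations in different settings can plausibly differ in level. One example is the share of patients who die where they wished, which research question 2 takes over from question 1a. For the patient CQ Index, a shift between inpatient and home care is also a shift between interview and postal completion.

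The results go back to project managers and stakeholders within two months of each measurement (Feedback and dissemination), partly to motivate further improvement. A mix artefact would therefore reach the people who decide what to change.

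Replacing the paired tests by unpaired ones would not cure this, because an unpaired test on pooled respondents still ignores organisation.

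**Working it through.** **1. The plan's own figures.** Lower targets × 2 periods × 17 trajectories: 15 × 2 × 17 = 510 patients and 30 × 2 × 17 = 1020 relatives per year. Over four years this is 510 × 4 = 2040 and 1020 × 4 = 4080. These match the article ("which gives a total number of about 2040 patients and 4080 bereaved relatives over four years"). The totals are sound, and nothing below changes them. The article gives no intraclass correlation (ICC), no number of organisations per trajectory and no between-organisation difference, so those are assumptions from here on.

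**2. Are the respondents the same people?** A relative eligible at month 0 reports a death 1.5 to 6 months earlier. At month 9 that death lies 10.5 to 15 months back, outside the window. For patients: "Patients are eligible if they have a life expectancy of less than six months and/or if they are undergoing palliative treatment". Some patients under palliative treatment might be asked twice nine months later, but few can be expected. So within-person pairing cannot hold the organisation mix constant. The mismatch between paired tests and unpaired data is a separate problem. Below, an unpaired test stands in for any workable version of the trajectory test.

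**3. How a shift enters.** With two organisations A and B and no change in either,

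spurious difference = (share of A at month 9 − share of A at month 0) × (level A − level B).

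- Assumed levels 80% and 60%: A's share from 50% to 70% gives 0.20 × 0.20 = +4 points; from 30% to 70%, +8 points; from 20% to 80%, +12 points. With 30 relatives per period, the chance of p < 0.05 is about 5%, 10% and 17%.
- Assumed levels 90% (home care) and 50% (hospital), 30 relatives, 20 hospital/10 home becoming 10/20: (20 × 0.5 + 10 × 0.9)/30 = 63%, then (10 × 0.5 + 20 × 0.9)/30 = 77%. As observed counts, 19/30 against 23/30 gives z = 0.133/√(0.7 × 0.3 × 2/30) = 1.13, p = 0.26. The bias is 13 points, yet this result would not be significant.

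**4. False-positive rate.** Simulation assumptions: five organisations, total SD 1, between-organisation variance equal to the ICC (0.05, 0.10, 0.20), no true change, two-sided 5% level, 15–20 patients or 30–40 relatives per period, 4000 runs per cell. The Monte Carlo standard error at 5% is √(0.05 × 0.95/4000) = 0.3 points.

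| Organisation shares | Pooled unpaired t test | Period + organisation |
|---|---|---|
| Same underlying shares, random arrival | about 5% | about 5% |
| Modest drift around common shares (Dirichlet concentration 20) | about 5–8% | about 5% |
| Redrawn independently each period (Dirichlet 1), patients | about 6–11% | about 5% |
| Redrawn independently each period (Dirichlet 1), relatives | about 7–18% | about 5% |

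The top of the last row needs an ICC of 0.20: about 14% at n = 30 and about 17–18% at n = 40. With exactly equal numbers per organisation at both periods, the pooled test at n = 30 is slightly conservative: 3.9% at ICC 0.10 and 3.3% at ICC 0.20.

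**The case against.** **Size.** The large rates require month 0 shares to say nothing about month 9 shares. Nothing in the article supports that. Where a trajectory has more than five organisations, those with the most eligible patients are chosen, which is a fairly stable feature. This stands: with stable shares the pooled test is about correctly sized, and the upper figures mark an extreme.

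**Stronger readings.** A reader might infer that the error bars for research question 2 are wrong whether the mix moves or not. That does not follow, because stable shares with random arrival give about 5%, and exactly fixed numbers give only slight conservatism. A reader might also infer that the test would declare any shift an effect. The 63% to 77% example, with p = 0.26, shows otherwise.

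**Scope.** Research question 2 is a secondary objective, is also analysed descriptively, and is read beside a process evaluation that looks for other explanations. The programme analysis is multilevel. This stands too: the point does not reach research question 1.

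**What an article leaves out.** Organisation numbers may be set in a full protocol that is not shown, and the word univariate does not itself say that respondents are pooled. Pairing on organisation means would remove the shift. But the article does state the trajectory-level target and the person-level type of test, and it gives no sign that organisation means are intended. The point rests on those statements, not on the absence of a quota.

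**Remedy.** With 15–20 patients over five organisations, each supplies about 3–4. Fixed quotas may be out of reach where, as the Discussion says, patients are scattered. This stands and shapes the fix.

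**Conclusion.** The point holds as a conditional weakness of the analysis for research question 2. Any shift in organisation mix passes in full into the trajectory contrast, and the stated analysis cannot separate it from change. How much this matters cannot be derived from the article. Under the assumptions above, the false-positive rate is near nominal with stable shares and modestly raised with drift. It is seriously raised only if the mix is redrawn freely and organisations differ strongly. The documents do not support the claim that the trajectory results are wrong in every case. The change is still worth making, because it is cheap and keeps the rate near 5% in every scenario tried.

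**What to change.** - For research question 2, compare month 9 with month 0 within organisations: a linear model with period plus organisation as a fixed factor, or a Mantel-Haenszel comparison stratified by organisation for percentages. Merge sparse organisations by setting. Stratification is safer than logistic regression with many organisation terms, where sparse cells risk separation.
- Report the number of respondents per organisation at both measurements, in the feedback reports as well, so that a shift is visible.
- Recruit in the same organisations at both measurements and aim for a similar split. Treat this as guidance, not as a fixed quota.

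Cost: with five organisations, four degrees of freedom (58 to 54 with 30 relatives per period; 28 to 24 with 15 patients). Some precision is lost in the smallest patient samples when the mix moves strongly, and organisations seen at only one measurement do not contribute. The recruitment totals stay as they are.

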### Effect evaluation

Pre-test and post-test measurements will take place in the effect evaluation, in month 0 and month 9 respectively (see Figure 2). During these two measurement months, eligible patients and bereaved relatives will be asked to participate.

**Figure 2 F2:**
[figure not shown]
Chronological overview of one year of the program.

#### Data collection

In the pre-test and post-test measurements, a set of quality indicators will be measured [20], making use of three types of measurement instruments:

•Numeric Rating Scales of six symptoms

•The Consumer Quality Index Palliative Care for patients

•The Consumer Quality Index Palliative Care for bereaved relatives

Numeric Rating Scales (NRS) will be used to measure the quality indicators ‘The % of patients with moderate to severe pain’, ‘The % of patients with moderate to severe fatigue’, ‘The % of patients with moderate to severe shortness of breath’, ‘The % of patients with moderate to severe constipation’, ‘The % of patients with moderate to severe anxiety’ and ‘The % of patients who feel moderately to severely depressed’. These indicators are associated with one specific programme objective, namely ‘Patients receive care for their needs in the physical and psychosocial domains’.

Patients will be reminded by one of their health care professionals to complete the NRS for the six symptoms (see Table 1) approximately the same time at three consecutive days. In principle, the patient will fill in the NRS scores. Only if the patient is not able to write will the health care professional assist the patient by writing down the NRS scores. The completed NRS forms will be collected by the health care professional after day 3 and send to the research team at the end of the measurement period.

**Table 1 T1:** Numeric rating scales of 6 symptoms

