**Symptoms (What number would you give your …symptom… on a scale of 0 to 10?**												
No pain	0	1	2	3	4	5	6	7	8	9	10	Much pain
No fatigue												Very fatigue
Not short of breath												Very short of breath
Not obstipated												Very obstipated
Not sad												Very sad
Not anxious												Very anxious

The Consumer Quality Index Palliative Care (CQ Index) is a validated questionnaire assessing quality indicators from the perspective of patients and bereaved relatives [21,22]. The quality indicators measured by this CQ Index are also directly related to the key objectives of the National Quality Improvement Programme (see Table 2). CQ index questions for instance concern patients’ or bereaved relatives’ experiences regarding the control over palliative care, the coordination of palliative care, the concordance between the care given and needs, preferences and values, and the physical, psychosocial and spiritual care received. In the version for bereaved relatives, questions are also asked about the actual and preferred place of death of the patient. The questionnaire version for patients consists of 56 items, while the version for bereaved relatives consists of 64 questions. Both questionnaire versions take approximately 30–45 minutes to complete. For inpatient patients, the questionnaire will be completed on the basis of an interview with a trained interviewer. Patients who receive care at home and bereaved relatives will receive the questionnaire by post to be completed and returned in a reply envelope to the research team. No reminders will be sent to non-responding patients, while a reminder will be sent after two weeks to non-responding bereaved relatives.

**Table 2 T2:** Key objectives of the national quality improvement program and associated quality indicators, measured with the CQ index palliative care

**Key objectives of the programme**	**Quality indicators measured with CQ index version for patients**	**Quality indicators measured with CQ index version for bereaved relatives**
Patients die at their preferred place	-	*Percentage of patients who died in the location of their preference
		*Extent to which patients in the last month before their death were in the location of their preference

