### Feedback and dissemination

The project manager and other stakeholders in a specific implementation trajectory will receive internal feedback reports on the results of the effect evaluation (after the pre-test measurements as well as after the post-test measurements) within two months after the measurement period. The prospect of getting feedback reports is important in order to increase the commitment of the project managers and stakeholders to participating in the measurements. In addition, the feedback reports will motivate the professionals involved to further improve the quality of their care, where needed.

Furthermore, interim reports about the progress of the programme as a whole will be published; these will also be made available to the general public. Also, additional international scientific publications about the effects and implementation of the programme are planned.

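### The six symptom indicators reach the research team through the care staff under evaluation, who know the period; a sealed and counted return, with the writer recorded, would be a cheap improvement

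*Protocol article*

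**What the plan says.** The effect evaluation compares month 0 with month 9 and has no control group (Protocol article, Abstract): "The effect evaluation has a pre-test post-test design, with measurements before implementation (month 0) and after implementation (month 9) of a best practice".

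The handling of the symptom scales is set out under Methods, Effect evaluation, Data collection:

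- Prompting: "Patients will be reminded by one of their health care professionals to complete the NRS for the six symptoms", at about the same time on three consecutive days.
- Completion: "In principle, the patient will fill in the NRS scores". The exception is: "Only if the patient is not able to write will the health care professional assist the patient by writing down the NRS scores".
- Collection and dispatch: "The completed NRS forms will be collected by the health care professional after day 3 and send to the research team at the end of" each measurement.

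The scores become six indicators, each the percentage of patients with a moderate to severe symptom. The article ties them to a single programme objective, on physical and psychosocial needs.

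The CQ Index takes another route in the same section. Inpatients complete it with a trained interviewer. For home patients and bereaved relatives it is posted and "returned in a reply envelope to the research team".

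Feedback and dissemination adds: "The project manager and other stakeholders in a specific implementation trajectory will receive internal feedback reports", after the pre-test and again after the post-test. One stated purpose is to motivate the professionals to improve their care.

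**The concern.** The estimate of interest for these indicators is the difference between two measurements. The people who prompt, sometimes write, collect and keep the forms belong to the care whose quality is being judged, and the calendar tells them which measurement it is. By month 9 they have worked with the best practice, and their trajectory has been due a report on its pre-test results.

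If staff record scores or return forms differently at month 9 than at month 0, the percentage with a moderate to severe symptom changes although symptoms have not. No concurrent comparison group would reveal this. The multilevel model named under Data analysis has levels for care network or organisation and for type of best practice, and neither separates a change in recording or return from a change in symptoms. The Discussion recognises that feedback reports may influence outcomes, but its response is to ask in the process evaluation about additional actions by care organisations, not about how scores were obtained or forms returned.

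**Working it through.** **The two routes side by side.** NRS: reminded by the patient's professional, written by that professional if the patient cannot write, then collected, held and sent by the professional. CQ Index: trained interviewer for inpatients; post and direct return for home patients and relatives. So the study already uses a route outside the care team for its other instrument.

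**Number of patients concerned** (Study population). The article's own total reproduces: 15 patients × 2 periods × 17 trajectories = 510 per year; × 4 years = 2040. One period alone is 15 × 17 × 4 = 1020. A distortion at post-test acts on that 1020.

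**Illustration.** The article gives no prevalence, non-return rate, share of patients needing a writer, or significance level. All of these are assumed below, with no true change, and one indicator is taken at a time.

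*Selective return.* Let p be the true share with a moderate to severe symptom and w the share of those patients' forms not returned, at post-test only. All other forms are returned.

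Observed share = p(1 − w) / (1 − pw)

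| p | w = 5% | w = 10% | w = 20% |
|---|---|---|---|
| 30% | 28.9% (fall 1.1) | 27.8% (fall 2.2) | 25.5% (fall 4.5) |
| 40% | 38.8% (fall 1.2) | 37.5% (fall 2.5) | 34.8% (fall 5.2) |
| 50% | 48.7% (fall 1.3) | 47.4% (fall 2.6) | 44.4% (fall 5.6) |

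Falls are in percentage points. Example: p = 40%, w = 10% gives 0.36 / 0.96 = 37.5%.

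*Shading by the writer.* Let a be the share of patients needing a writer and s the share of their moderate-to-severe scores recorded below the cut-off, at post-test only.

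Fall = p × a × s

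- Smallest case: 0.30 × 0.10 × 0.10 = 0.3 points.
- Largest case: 0.50 × 0.30 × 0.20 = 3.0 points.

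*Effect on a test.* Take two independent groups, 1020 patients at pre-test and 1020 at post-test less the forms withheld, with a two-sided 5% level and clustering ignored. The chance of a falsely significant fall is then about 8% for w = 5%, 19–22% for w = 10% and 60–69% for w = 20%, against a nominal 2.5%. For shading it runs from 3.5% to 27%. The planned multilevel model could give other figures. The point is that a larger sample does not dilute a systematic shift.

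*One trajectory.* Suppose 8 of 20 patients have the symptom (40%). If one of those eight forms is not returned (12.5%), the figure becomes 7/19 = 36.8%, a fall of 3.2 points.

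**The case against.** The case on the other side is substantial, and much of it limits the point.

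- *A reader might infer that the forms lie open in staff hands.* The article does not say so; it mentions no sealing for the NRS. Sealing, numbering and logs are details that a condensed article may leave to the full protocol, so their absence is not the point made here. The point is the stated route. Even a sealed form can go unsent, and a professional sees any score that he or she writes.
- *A reader might infer that patients understate symptoms because a carer collects the form.* One procedure is described for both measurements, so such an effect would be present at month 0 too and would largely cancel in the difference. Given the eligibility criteria, many month-9 patients are probably new and have no earlier result to react to. Nothing in the article suggests that self-completing patients would understate only at post-test, so a shift applied to all symptomatic patients is not supported. This objection stands.
- *Staff write only for patients who cannot.* This stands, and is why the shading range is the smaller one.
- *Withholding means holding back a record.* One form carries all six symptoms, so selection would act on patients rather than on single indicators, and there is no evidence that it happens. This stands.
- *Direction.* Some best practices, such as the tool for nursing assistants described in the Background, aim to identify needs better. Staff using it might encourage fuller reporting and raise post-test scores. This stands.
- *Feedback.* Its named recipients are the project manager and other stakeholders. Nurses and doctors are given as examples of stakeholders under Process evaluation, but the article does not say that the person collecting forms receives a report. Knowledge of the period does not depend on this.

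None of this removes the stated fact that the evaluated staff control recording for some patients and return for all.

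**Conclusion.** The point holds as a cheap improvement to a stated procedure. The six NRS indicators pass through staff who are part of the care evaluated and who know the period. In an uncontrolled comparison, differential recording or selective return at month 9 could not be told apart from a programme effect.

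The scope is six indicators under one programme objective and about 1020 post-test patients. It would be tempting to say that all 2040 patients are affected, but that total counts both measurements. The CQ Index indicators, which cover all five objectives, are not concerned.

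Under the assumed prevalence of 30–50%, the illustrative spurious fall is about 1.1 to 5.6 points through selective return and 0.3 to 3.0 points through shading by a writer. These figures rest wholly on assumed rates and on one assumed direction. They show what modest differences between periods could do. They are not evidence that scores are shaded or forms withheld.

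**What to change.** 1. Give each patient a pre-numbered NRS form with an envelope that the patient seals after day 3 and that reaches the research team unopened.
2. Count forms issued and forms returned at both measurements, and report the return rate by period.
3. Add a box on the form stating who wrote the scores.
4. Repeat the pre-post comparison on self-written forms as a sensitivity analysis.

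Steps 1 and 2 address return; steps 3 and 4 address recording. Step 4 is restricted to patients able to write, so the share of self-written forms should be shown for each period beside it.

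The cost is envelopes, numbering, one tick box and a little extra analysis. The downside is that staff do not see the study form. The reminders and the help for patients who cannot write can stay as described, so no additional visits are needed.
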